### Interim analyses {21b}

Not applicable as no interim analyses is planned for the ongoing study.

### Methods for additional analyses (e.g., subgroup analyses) {20b}

A recent clinical crossover trial has shown the beneficial effects of short-term FCV compared to conventional volume-controlled ventilation with respect to regional ventilation distribution in obese patients with a BMI ≥ 30 kg/m^2^ [7]. Therefore, we plan to conduct a subgroup analysis to compare the effect of individualized FCV or best clinical practice PCV on perioperative lung function, EIT data, and PPCs as well as PEPCs in the setting of perioperative mid-term ventilation of obese patients with a BMI ≥ 30 kg/m^2^ in cardiac surgery. In accordance with the results of Weber et al. [7] we do not only anticipate an enhancement of dorsal ventilation distribution but also of lung oxygenation indices at least after CPB when ventilating with FCV compared to PCV. The analyses on outcome parameters like oxygenation indices, EIT data, PPCs, and PEPCs will be carried out in an explorative approach as only few or no data exist until now. However, in accordance with {20a} for all continuous endpoints, a linear regression model using the intervention group as an independent variable and, for all binary secondary outcomes, logistic regression models will be fitted.

### Methods in analysis to handle protocol non-adherence and any statistical methods to handle missing data {20c}

In this first larger trial of mid-term FCV application in high-risk cardiac surgery procedures, more than one cardiopulmonary bypass time, intraoperative death, and/or cardiopulmonary resuscitation which are exclusively due to major intraoperative surgical complications as well as study protocol deviations with respect to the allocated intervention for more than 5 min (see {11d}) are defined as stop criteria. It is almost impossible that the perioperative ventilatory mode has an impact on the etiology of these stop criteria, especially as lungs are not being ventilated during CPB in the current study protocol. However, major surgical complications leading to the defined stop criteria and the incidence of the criteria itself significantly affect postoperative patient outcomes. Thus, these patients will be excluded from data analysis whereas all other participant data will be analyzed “as randomized” following an intention-to-treat analysis.

Due to the nature of the intervention and the collection of predominantly short-term data, there will be very few missing data regarding secondary outcomes and (nearly) no missing data with respect to the primary endpoint. Since in most cases these will be due to operational disturbances, loss of paper CRFs, and laboratory errors, missing data can be assumed to be completely missing at random. As the omitting of the (few) missing values will not lead to bias this approach will be utilized for this trial.

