#### Other objectives of exploratory ancillary studies

To determine how an individualized perioperative FCV approach compared to best clinical practice PCV affectsthe perioperative distribution of air within the thoracic cavity. Data are collected by electrical impedance tomography (EIT) before induction of general anesthesia, during pre- and postoperative mechanical ventilation and postoperative spontaneous breathing. Consequently, different EIT-derived parameters will be analyzed (EIT sub-study, see {12}).perioperative right ventricular function. Functional parameters are assessed by perioperative transthoracic (TTE) or transesophageal (TEE) echocardiography prior to induction of general anesthesia under spontaneous breathing as well as before and after CPB (echocardiography sub-study, see {12}). As mechanical ventilation compromises the pre- and afterload of the right ventricle [14], this question arises when considering the contrary intrathoracic pressure course during FCV compared to PCV (Fig. 1). Additionally, in on-pump cardiac surgery procedures, the right heart is also affected by ischemia–reperfusion injury which impacts on echocardiographic right functional parameters itself [15].

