#### Postoperative respiratory settings

After postoperative admission on the ICU under invasive ventilation, another incremental PEEP trial is conducted in the PCV and PEEP + DP trial in the FCV group in order to individualize group-specific ventilation according to the postoperative condition and the upright patient position of 30–45°. In the ICU, PCV is delivered through the BIPAP modus for patient safety and comfort by default. FiO_2_ is reduced to not less than 0.4 depending on the individual oxygenation capacities.

Patient weaning of invasive ventilation is initiated 3–4 h after CPB end in the case of no new postoperative hemodynamic instability, excessive drainage loss nor gross new pathologies according to the postoperative chest x-ray with the need for intervention. For initiation of weaning continuous propofol infusion is stopped and piritramide (0.1–0.15 mg/kg actual body weight) is administered i.v. If respiratory weaning cannot be commenced due to the above-mentioned criteria, group-specific ventilation will be maintained for up to 24 h after CPB. If the participant still fails extubation by that time, ventilatory settings will be at the discretion of the intensivist in charge and not controlled by study personnel any longer.

PEEP and DP trials, as well as pre- and intraoperative interventions, are all administered and conducted by the same anesthesiologist being in charge of protocol adherence together with a specially trained senior cardiac anesthesiologist.

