### Relevant concomitant care permitted or prohibited during the trial {11d}

If a participant requires cardiopulmonary resuscitation during the group-specific ventilation, it is mandatory that the ventilation mode is changed to volume-controlled in order to assure a sufficient V_t_. The violation of the designated perioperative ventilation protocol due to this incident or any other operational disturbances for more than 5 min will be reported as an adverse event and is additionally defined as a study stop criterion. As further study stop criteria, we determined more than one cardiopulmonary bypass time and intraoperative death solely due to major surgical complications.

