### Sample size {14}

The sample size was calculated according to the study hypothesis. Based on the previous results of protective ventilation protocols in the setting of on-pump cardiac surgery [21, 22], the effect size of the intervention on postoperative plasmatic IL-8 concentrations was estimated as moderate being well aware about the exploratory nature of this study of mid-term clinical FCV utilization. Under these assumptions (Cohen’s d = 0.5), the total sample size required to achieve a power of 1-β = 0.8 for a two-sample *t*-test at a two-sided level α = 0.05 resulted in 2*64 = 128 [36]. As the primary endpoint is obtained 6 h after termination of CPB, most dropouts will be due to a second cardiopulmonary bypass phase within this time frame or other in {11d} defined stop criteria in estimated 10% or less of the cases. Therefore, an additional 10% of patients will be randomized summing up to a total sample size of 128*1.1 = 140.8 ≈ 140 randomized study participants.

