## Assignment of interventions: allocation

### Sequence generation {16a}

Randomization to the control (PCV) or intervention (FCV) group is performed by a computer-generated schedule with an 1:1 allocation using permuted blocks of lengths 4 and 6 in order to ensure sufficient concealment.

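### Randomised patients who meet a stop criterion, including more than 5 min off the allocated ventilation, are dropped from an analysis labelled intention-to-treat, and no analysis of all randomised patients is stated

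*Protocol article*

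**What the plan says.** Section {20c} of the protocol article lists the stop criteria: more than one bypass period, intraoperative death or resuscitation caused exclusively by major surgical complications, and departures from the allocated intervention lasting more than 5 min. It then states: "Thus, these patients will be excluded from data analysis whereas all other participant data will be analyzed" in the randomised groups, and calls this intention-to-treat. The reason offered is: "It is almost impossible that the perioperative ventilatory mode has an impact on the etiology of these stop criteria". The section adds that the lungs are not ventilated during bypass, and that the complications and the criteria themselves markedly affect outcome.

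Section {11d} gives the source of the 5 min criterion. A violation of the ventilation protocol due to resuscitation or "any other operational disturbances for more than 5 min will be reported as an adverse event", and is also a stop criterion. Section {14} counts all stop criteria in {11d} among the dropouts, put at 10% or less. Under Postoperative respiratory settings, a patient who cannot yet be weaned stays in the comparison: "group-specific ventilation will be maintained for up to 24 h after CPB". Section {22} says that events meeting stop criteria, and protocol violations from operational disturbances, will be reported and published with the main results.

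**The concern.** Intention-to-treat keeps patients in the analysis whatever happens to their treatment after allocation. Here, failure to keep to the allocated ventilation is itself a ground for removal. That criterion is tied to the mode under test: the arms use different respirators (section {17a}), and the FCV arm has an additional tube adapter (General setting under {11a}). Care providers and assessors are not blinded during group-specific ventilation. Because that ventilation can run to 24 h after bypass, a patient whose 6 h IL-8 sample has already been taken can still be removed.

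The primary IL-8 comparison is at stake, and so are the comparisons of pulmonary (PPC) and extra-pulmonary (PEPC) complications, which section {22} also uses as the harm outcomes. If the two arms lose patients at different rates, or lose different kinds of patient, those who remain are no longer comparable by randomisation.

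**Working it through.** **The plan's own figures.** Section {14} assumes "d = 0.5), the total sample size required to achieve a power of 1-β = 0.8" with a two-sample t-test "at a two-sided level α = 0.05 resulted in 2*64 = 128". Solving for that test gives 63.77, so 64 per arm and 128 in total, which agrees. Then 128 × 1.1 = 140.8, stated as 140, or 70 per arm under the 1:1 allocation in {16a}.

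**Does the rationale reach each criterion?**
- Second bypass, intraoperative death and resuscitation of purely surgical cause: the argument in {20c} is directed at these.
- Deviation from allocated ventilation of more than 5 min: neither the surgical argument nor the remark about bypass applies. Such a deviation can occur at any time during group-specific ventilation, before or after bypass.

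**Bias formula.** Let e be the share excluded in an arm, and let excluded patients have IL-8 higher by D (in SD units) than those retained in the same arm. The mean of all randomised patients in the arm is then the retained mean plus e × D. If the arms do not differ among all randomised patients, the retained comparison is off by

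bias (FCV − PCV) = −(e_FCV − e_PCV) × D.

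Standard error in SD units: √(1/n_FCV + 1/n_PCV), with n = 70 × (1 − e). The two-sided error at α = 0.05 comes from the noncentral t distribution with noncentrality bias/SE.

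**Assumed inputs.** The protocol gives only an overall ceiling of 10%, with no split by arm and no D. Take 12% v 4%, which is 8.4 + 2.8 = 11.2 of 140, or 8% overall and inside the ceiling. Then n_FCV = 61.6, n_PCV = 67.2 and SE = √(1/61.6 + 1/67.2) = 0.176.

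| D (SD) | Bias (SD) | Share of d = 0.5 | Two-sided error |
|---|---|---|---|
| 0.25 | −0.08 × 0.25 = −0.02 | 4% | 5.2% |
| 0.5 | −0.04 | 8% | 5.6% |
| 1 | −0.08 | 16% | 7.4% |
| 1.5 | −0.12 | 24% | 10.4% |
| 2 | −0.16 | 32% | 14.7% |

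**Other assumed patterns.**
- 10% v 10%, same D: bias 0, error 5.0%.
- 10% v 5%, D from 0.5 to 1.5: bias −0.025 to −0.075, error 5.2% to 7.1%.
- 15% v 5%, D from 0.5 to 1.5: bias −0.05 to −0.15, error 5.9% to 13.3%.
- Equal numbers but different prognosis, 10% per arm with D = 1 in FCV and 0 in PCV: bias −(0.10 × 1 − 0.10 × 0) = −0.10, error 8.6%.

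Swapping the arms reverses the sign and leaves the error unchanged. A simulation of 20,000 trials at 15% v 5% and D = 1 gave 8.4% error after exclusion and 5.2% with all randomised patients analysed.

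**Power.** At d = 0.5, all 140 give 83.6%. With 10% excluded (63 per arm) it is 79.5%. Keeping the patients therefore needs no larger sample, before allowing for any extra variance they bring.

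**The case against.** The best defence is that the surgical criteria are reasonably argued in {20c}, that a patient who dies in theatre has no 6 h sample, and that the violations are not hidden, since {11d} makes them reportable adverse events and {22} promises publication. All of that stands. It does not return the patients to the IL-8, PPC or PEPC comparisons, and it does not make the population intention-to-treat.

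The size is also fairly disputed. An imbalance between arms would most naturally come from equipment, whereas a large IL-8 excess is more plausible after a surgical catastrophe; putting both at the high end combines two different groups of patients. Device failures unrelated to prognosis and to IL-8 would cause no bias. If failures themselves raised IL-8 in one arm, the effect among all randomised patients would not be null, and the error figures would not be type I errors. This is why the range starts near 5%.

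A reader might infer more than the text supports:
- That FCV has more device problems, so the rule favours FCV. The protocol shows only that the equipment differs.
- That failures vanish from the harm record. Sections {11d} and {22} say otherwise.
- That the remark beginning "As mechanical ventilation compromises the pre- and afterload of the right ventricle" shows ventilation mode leading to resuscitation or a return to bypass. It motivates an exploratory sub-study, and the link to those events is an inference.
- That {11d} and {20c} contradict each other on the second bypass. In {11d} the qualifier about surgical cause can be read as covering both the second bypass and death.
- That many valid samples would be lost. Weaning starts 3–4 h after bypass, and {17a} expects most patients to be weaning or extubated by 6 h, so late removals are possible but probably uncommon. The 5 min limit can be checked against the electronic records named in {11c}.

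**Conclusion.** The label is wrong as written, and this does not depend on any assumption. Section {20c} removes randomised patients for events after randomisation, including non-adherence to the allocated ventilation, and no analysis of all randomised patients is stated. The stated rationale does not cover the deviation criterion, which is where the point is strongest.

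Bias is possible, not demonstrated. It requires exclusions that differ between arms in number or in prognosis, and its direction follows whichever arm loses more poor-prognosis patients. Under the assumed 12% v 4% with D from 0.25 to 2 SD, it is 0.02 to 0.16 SD (4% to 32% of the planned effect), with a two-sided type I error of about 5% to 15%. With equal exclusion of similar patients it is zero.

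The two lists of criteria also need reconciling, chiefly on resuscitation. In {11d} the criterion is a protocol violation of more than 5 min due to any resuscitation during group-specific ventilation; in {20c} resuscitation of exclusively surgical cause is a criterion in its own right.

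**What to change.** Amend {20c} and {11d} before the data are analysed:

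1. Primary analysis: every randomised patient with a 6 h IL-8 value, in the allocated arm. Analyse secondary outcomes, including PPCs and PEPCs, on the same principle.
2. Continue outcome collection after a stop criterion where possible. This concerns data only and implies no rule on whether ventilation continues.
3. State how IL-8 values missing because of intraoperative death are handled, and which bypass end anchors the 6 h sample after a second bypass.
4. Keep the present exclusion as a sensitivity analysis, labelled as such and not as intention-to-treat, with exclusions tabulated by arm and reason.
5. Remove the claim that ventilation mode cannot be a cause as a justification for the deviation criterion.
6. Use one list of stop criteria in both sections, with the resuscitation wording reconciled and the scope of the surgical-cause qualifier made explicit.

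The cost is a text amendment and some further sampling in patients who are already in hospital. No additional patients are needed. The downside is somewhat more outcome variance from complicated cases, which would take back part of the power gained by keeping them.

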#### Key secondary objectives of the main study

To determine whether FCV compared to PCV benefits the perioperative lung function with respect to oxygenation and decarboxylation capacities, the incidence of PPCs and postoperative extra-pulmonary complications (PEPCs), weaning times from mechanical ventilation and duration of intensive/intermediate care unit stays and time to discharge.

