## Assignment of interventions: blinding

### Who will be blinded {17a}

Due to application of interventions with different respirators and ventilatory equipment, care providers and assessors cannot be blinded during group-specific mechanical ventilation in FLOWVENTIN HEARTSURG. However, trial participants are blinded at any time point until individual trial close-out after 6 months post-surgery.

As soon as the patients are extubated, blinding of at least study assessors is possible. At the earliest, this can be achieved 6 h after CPB as most patients are in the process of weaning or already extubated. At the latest from 24 h after CPB onwards, all involved study assessors are masked as well as data analysts at a later time. Blinding of these parties is not lifted before a fixed data set of each outcome parameter is created.

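### Ventilator-derived outcomes after weaning starts exist only in patients not yet weaned, so the rule of few values missing, completely at random and safely omitted does not fit them

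*Protocol article*

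**What the plan says.** - **Outcome window.** In Important secondary outcomes of the main study, {12}, ventilation pressures, dynamic compliance, airway resistances and mechanical power run up to 24 h after CPB.
- **Start of weaning.** Postoperative respiratory settings, {11a}: "Patient weaning of invasive ventilation is initiated 3–4 h after CPB end in the case of no new postoperative hemodynamic instability". Excessive drainage loss and gross new findings on the chest film also delay it.
- **Who stays ventilated.** Same section: "If respiratory weaning cannot be commenced due to the above-mentioned criteria, group-specific ventilation will be maintained for up to 24 h after CPB".
- **Status at 6 h.** Section {17a}, on when assessors can first be blinded: "this can be achieved 6 h after CPB as most patients are in the process of weaning or already extubated". No percentage is given.
- **Weaning as an outcome.** The key secondary objectives, {7}, compare the arms on "weaning times from mechanical ventilation and duration of intensive/intermediate care unit stays and time to discharge".
- **Analysis.** Section {20a} fits a linear regression on group and EuroSCORE II to all continuous secondary endpoints, with a Bonferroni adjustment across secondary outcomes.
- **Missing data.** Section {20c} expects very few missing secondary values, attributes most of them to operational disturbances, lost forms and laboratory errors, concludes that "missing data can be assumed to be completely missing at random", and then: "As the omitting of the (few) missing values will not lead to bias this approach will be utilized".

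**The concern.** A driving pressure or a mechanical power of ventilation does not exist in an extubated patient. By the protocol's own timetable, these measures start to disappear 3–4 h after CPB and are absent in a large share of patients for much of the 24 h window. The reason is that the patient met the clinical conditions for weaning, not that a form was lost. Section {20c} does not name extubation as a cause of absent values. Its rule is also the only one the article gives.

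If values after weaning starts are regressed on group, each arm is represented by its not-yet-weaned patients. Membership of that subset is decided after randomisation, by clinical condition and by a process the intervention may change. If FCV shortened weaning, its remaining patients would be the more severely ill and FCV would look worse on these measures. If FCV lengthened weaning, it would look better. Lower mechanical power is the stated rationale for FCV, and the Background says clinical data on it are lacking, so readers will look closely at this outcome.

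**Working it through.** **1. The plan's own figure.** Section {14} uses d = 0.5, two-sided α = 0.05 and power 0.80. The two-sample t-test needs 63.77, so 64 per arm and 128 in total; 128 × 1.1 = 140.8, taken as 140, or 70 per arm. This reproduces and is not in dispute. It is used below only for counts.

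**2. The passages side by side.**

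| Period | Who has group-specific ventilator values | Does the {20c} rule fit? |
|---|---|---|
| T−2, T−1, T0, after re-individualisation in the ICU | essentially all patients | yes, for values truly lost |
| from 3–4 h after CPB | those in whom weaning has not begun | no |
| about 6 h to 24 h | a minority, kept ventilated for clinical reasons | no |

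The ancillary EIT schedule in {12} adds that weaning runs on pressure support at one set of settings, given without distinction by arm. Values recorded then would not reflect the allocated mode either.

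**3. How many would contribute.** The share still ventilated is not in the documents; the fractions f are assumptions. With n = 70 × f per arm and the t-test power for d = 0.5 at α = 0.05:

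| f | n per arm | power |
|---|---|---|
| 50% | 35 | 0.54 |
| 25% | 17.5 | 0.30 |
| 10% | 7 | 0.14 |
| 5% | 3.5 | 0.09 |

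These powers are before any Bonferroni adjustment.

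**4. Illustration A: selection by odds of extubation.** Every parameter is an assumption. Severity u is standard normal. Compliance correlates −0.6 with u and has no true group effect. The log-odds of being extubated are a − 1.5u, plus a shift s in the FCV arm. The contrast is taken among those still ventilated, with 19–50% of the PCV arm still ventilated.

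| s | odds ratio exp(s) | FCV − PCV among those still ventilated |
|---|---|---|
| 0 | 1.0 | 0 SD |
| 0.3 | 1.35 | about −0.03 to −0.04 SD |
| 0.7 | 2.0 | about −0.08 SD |
| 1.0 | 2.7 | about −0.11 to −0.12 SD |

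At s = 0 the contrast is unbiased, but the ventilated patients still lie about 0.32–0.55 SD below the full cohort. Late values would then not describe the trial population.

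**5. Illustration B: selection by extubation time.** Extubation time is log-normal with a median of 6 h in PCV and a log-SD of 0.5. The ventilator measure correlates 0.5 with severity and has no true group effect.

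- Extubation unrelated to severity: no bias.
- Severity–extubation correlation 0.5–0.8, equal weaning: no group difference, but those still ventilated deviate from the full cohort by 0.20–0.32 SD at 6 h and 0.46–0.74 SD at 12 h.
- Same correlations, FCV weaning times 20–33% shorter: a spurious group difference of 0.08–0.23 SD at 6 h and 0.10–0.28 SD at 12 h, with about 6 PCV and 1–2 FCV patients left at 12 h.

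Neither model includes EuroSCORE II.

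**6. Effect on a test.** With 64 evaluable per arm and 20–50% still ventilated, n is about 13–32 per arm. A bias of 0.12 SD then raises the two-sided rejection rate from 5% to about 6.0% (n = 13) or 7.6% (n = 32), unadjusted.

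**The case against.** The strongest reply is that a driving pressure after extubation is undefined, not missing. Section {20c} speaks of data lost through disturbances, forms and laboratory errors, and never says that values after extubation fall under its rule. This stands. It narrows the point: the rule does not separate structural absence from loss, and nothing else in the article covers these values.

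Second, a reader might infer that the trial plans a between-arm test at every hour to 24 h. The documents do not say so. The 24 h limit matches the limit on group-specific ventilation, so it can be read as while ventilated and at most 24 h. The recording times are in Table 1, which is not shown, and {20a} does not say whether repeated values are modelled by time point or summarised per patient. What stands is that {20a} covers all continuous secondary endpoints and nothing restricts the ventilator measures to the period before weaning.

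Third, a reader might infer that the late comparisons are shown to be biased. They are not. Bias between arms needs extubation that depends on severity and also weaning that differs by arm; with equal weaning it is zero. Under the assumptions of illustration A it is small beside the loss of precision, and EuroSCORE II may remove part of it.

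**Conclusion.** The point holds for ventilator-derived secondary outcomes after weaning starts, and only there. For them, the assumption of few values absent completely at random cannot be carried over, and the assurance that omission is harmless is unsupported. Presence of a value depends on clinical condition and on weaning time, so an arm comparison in that period is not protected by randomisation.

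The direction of any bias depends on which arm weans faster. Its size cannot be derived from the documents: 0 SD with equal weaning, about 0.1 SD under an assumed two- to threefold difference in the odds of extubation, and up to 0.28 SD at 12 h under the strongest assumptions tried. Low numbers are the more certain consequence.

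The primary endpoint is untouched by this mechanism, because IL-8 at 6 h is measured in blood from a central venous catheter and can be obtained after extubation. Pre- and intraoperative ventilator values are also untouched. The change should be made, but the trial's main conclusion does not depend on it.

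**What to change.** 1. In {12} or {20a}, limit between-arm tests of airway pressures, driving pressure, dynamic compliance, resistance and mechanical power to time points before weaning starts: T−2, T−1, T0 and after re-individualisation in the ICU.
2. Report later values descriptively, with the number still ventilated per arm at each time point. If they would otherwise have been tested, they then leave the Bonferroni family.
3. In {20c}, limit the completely-at-random assumption and the omission rule to values that should exist but were lost. State separately that values after extubation or death are undefined.

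The cost is analysis wording only; treatment, visits and data collection do not change. The downside is that late ventilator values become descriptive.

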### Plans to promote participant retention and complete follow-up {18b}

Patients are allowed to withdraw study participation at any time and for any reason. However, as interventions are only applied when the patient is under general anesthesia and most study data are collected within the first 24 h after CPB while the patient is being either under general anesthesia or shortly after awakening from an open chest cardiac surgery procedure, withdrawal rate taking together with the dropout rate (see {14}) and missing data is thought to be less than 10% of the cases during the whole study period.

In order to reduce the risk of loss to follow-up during phone surveys up to 6 months post-surgery, at least one phone number of a close relative is recorded at the time of recruitment.

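### The claim that all missing data are completely at random, so that omission causes no bias, rests on technical causes and does not cover withdrawal or loss at the 1- and 6-month phone surveys

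*Protocol article*

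**What the plan says.** Section {20c} of the protocol article sets one rule for all outcomes. It expects that "there will be very few missing data regarding secondary outcomes and (nearly) no missing data with respect to the primary endpoint". It explains the gaps by saying that "in most cases these will be due to operational disturbances, loss of paper CRFs, and laboratory errors", and infers that "missing data can be assumed to be completely missing at random". The handling follows: "As the omitting of the (few) missing values will not lead to bias this approach will be utilized for this trial". The section describes no sensitivity analysis.

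Two other sections bear on this.

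- Section {18b} puts withdrawal, dropout and missing data together: "missing data is thought to be less than 10% of the cases during the whole study period". It also recognises a follow-up problem and a measure against it. "In order to reduce the risk of loss to follow-up during phone surveys up to 6 months post-surgery", the trial records at least one close relative's phone number at recruitment.
- Section {12} lists hospital readmission and mortality at one and six months among the important secondary outcomes and gives the phone surveys as their source. Under section {20a}, binary outcomes are analysed by logistic regression on arm and EuroSCORE II.

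**The concern.** The inference is wider than its premise. A statement about the cause of most gaps cannot support a no-bias claim for all of them. The causes listed (disturbances in operation, lost paper forms, laboratory errors) belong to the perioperative and laboratory phase. They say nothing about a patient who withdraws, or whom the surveyor cannot reach at one or six months. The supporting argument that the data are mainly short-term does not apply to these outcomes either.

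For the phone outcomes the missingness is plausibly related to the value that is missing, because a patient who has died or is back in hospital is harder to reach. Complete-case analysis then tends to lose events more often than non-events. The event rates come out too low. If the selective loss also differs between arms, the treatment comparison is biased as well. Late event counts are likely to be small in a trial of 140, so a few unknown patients can matter. A reader who accepts the no-bias sentence would not be warned of this.

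**Working it through.** **The plan's own figures.** The missing-data rule has no figure to reproduce. The sample size in section {14} does reproduce: a two-sample t-test with d = 0.5, two-sided alpha 0.05 and power 0.80 needs 63.77, hence 64 per arm (power 0.801), and 128 × 1.1 = 140.8, taken as 140. At 1:1 this is 70 per arm. Ten percent of 140 is 14 patients.

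**Stated causes against possible causes.**

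| Cause of missing data | Used in {20c} to justify the claim? | Plausible link to the outcome? |
|---|---|---|
| Lost paper case report forms | yes | none evident |
| Laboratory error (one staff member unaware of arm, {18a}) | yes | none evident |
| Operational disturbances | yes | link to arm possible (different respirators, {17a}); none shown to outcome |
| Withdrawal ({18b}) | no | possible |
| Loss at the phone surveys ({18b}) | no | yes, for death and readmission |

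**Phone outcomes.** Let p be the true risk, and let e and n be the probabilities of being missing for patients with and without the event.

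- Observed risk = p(1 − e) / [p(1 − e) + (1 − p)(1 − n)].
- Observed odds = true odds × (1 − e)/(1 − n).
- The odds ratio (OR) is therefore multiplied by the ratio of (1 − e)/(1 − n) in FCV to that in PCV. If e and n are the same in both arms, the factor is 1.

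Assumed scenarios, with no true effect and n = 5% in both arms:

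| e in FCV | e in PCV | OR | Observed FCV vs PCV risk at true 5%, 10%, 20% |
|---|---|---|---|
| 5% | 5% | 1.00 | equal to the true risk |
| 30% | 30% | 1.00 | 3.7%, 7.6%, 15.6% in both arms |
| 30% | 5% | 0.70/0.95 = 0.74 | 3.7 vs 5.0; 7.6 vs 10.0; 15.6 vs 20.0 |
| 50% | 5% | 0.50/0.95 = 0.53 | 2.7 vs 5.0; 5.5 vs 10.0; 11.6 vs 20.0 |

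Swapping the arms would invert the ratio.

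A milder assumption is that 12% are missing in one arm and 6% in the other, and that missing patients have k times the risk r of observed patients. With a true risk of 5% in both arms, r = 0.05/[(1 − m) + km].

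- k = 3: 0.05/1.24 = 4.0% against 0.05/1.12 = 4.5%, a gap of 0.4 points.
- k = 5: 0.05/1.48 = 3.4% against 0.05/1.24 = 4.0%, a gap of 0.65 points.

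The standard error of a risk difference with about 65 per arm at 5% is √(2 × 0.05 × 0.95/65) = 3.8 points, so this shift is small. The effect on the level of risk is larger. With 10% missing, the share of deaths lost is km/[(1 − m) + km], which is 0.3/1.2 = 25% for k = 3 and 0.5/1.4 = 36% for k = 5.

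Extreme bounds, with the unknown patients in one arm all counted as events and those in the other arm as none, move the risk difference by 2/70 = 2.9, 4/70 = 5.7 or 7/70 = 10 points for 2, 4 or 7 unknown patients per arm.

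**Primary endpoint.** If a fraction m is missing in one arm only and those patients lie k SD above their arm mean, the bias is −mk/(1 − m).

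- m = 2%, k = 1: −0.02 SD, type I error 0.052.
- m = 10%, k = 1: −0.11 SD, type I error 0.098.
- Equal m and k in both arms: 0.

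The planned effect is 0.5 SD. The protocol expects almost no missing values here, so the first line is the relevant one.

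**The case against.** The case for leaving the text alone has real strength, and much of it stands.

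- **No phone-loss rate is given.** The figure below 10% in {18b} is an expected total of withdrawal, dropout and missing data. Section {14} already assigns an estimated 10% or less mainly to second bypass runs and other stop criteria, and those patients are excluded, not unknown. Seven unknown patients per arm is therefore an upper extreme, not something the plan allows for.
- **The comparison is fairly robust.** Loss that depends on arm alone does not bias a model that contains arm. Loss that depends on the event alone leaves the odds ratio unchanged. Participants are blinded until close-out at six months ({17a}), which weakens any reason for selective loss to differ by arm.
- **There is some protection already.** A death reported by the recorded relative is an observed event, and nothing in the protocol says that known deaths are dropped.

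Two stronger readings are tempting, and the documents support neither. A reader might infer that the major ventilation disturbances described in {11d} enter through the missing-data rule and bias it by arm. But "any other operational disturbances for more than 5 min will be reported as an adverse event and is additionally defined as a study stop criterion", and {20c} removes patients who meet a stop criterion under a separate exclusion. That exclusion is a different question. A reader might also infer that {20c} forbids any check of the assumption. It states an assumption and a method and names no check, but it prohibits none, and an analysis plan that is not shown may contain one.

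What the objection does not answer is the gap in the reasoning. The no-bias statement is unconditional, and its stated grounds do not cover the two sources of loss that {18b} itself recognises.

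**Conclusion.** The concern holds for readmission and mortality at one and six months. The statement that omission causes no bias is unsupported there, because the cited causes are technical and cover only most cases. Event rates can be understated: a true 10% would be seen as 7.6% if 30% of events and 5% of non-events were lost. The comparison is biased only if event-related loss also differs by arm. Odds ratios of 0.74 to 0.53 under no effect require 30% to 50% of events to be lost in one arm against 5% in the other. All of these missingness rates and risks are assumptions, since the documents give none for the surveys.

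A reader might extend the criticism to the primary endpoint. The documents do not support that. IL-8 at 6 h is expected to be nearly complete, and 2% missing in one arm would shift the result by about 0.02 SD against a planned 0.5 SD. The point is worth correcting because it affects what can be concluded from the late outcomes. It does not threaten the main result.

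**What to change.** 1. In {20c}, limit the completely-at-random and no-bias statement to technical losses, that is, lost case report forms and laboratory errors. State that it is not assumed for withdrawal or for loss at the phone surveys.
2. Tabulate missing values by arm and reason for each outcome. This would also show any imbalance from short operational disturbances that do not meet the stop criterion.
3. For readmission and mortality at one and six months, use the relative's number already recorded to settle vital status before a patient is classed as missing. Keep the complete-case result and add a best/worst-case or delta-adjusted sensitivity analysis beside it.
4. Optionally, add multiple imputation or a mixed model using the patient's other IL-8 samples as a sensitivity analysis for the primary endpoint. This has low priority at the missingness expected.

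The cost is a change of wording, a little more analysis work, and wider stated uncertainty for the late outcomes. The primary analysis and the sample size stay as they are.
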